#### Final Common Procedure for Both Groups

A metallic femoral head will be introduced and impacted on the Morse taper of the stem. The hip will then be reduced, followed by a final check of stability at the extremes of the ROM, as well as evaluation of limb length and soft tissue tension.

For closure, 2 holes will be drilled in the greater trochanter using a 2.5-mm drill for reinsertion of the external rotators and posterior hip capsule. Ethibond sutures will be tightened for a transosseous repair of the external rotator capsule in anatomical position. The fascia lata will be closed with X-shaped Vicryl® 2.0 separate stitches. The subcutaneous layer will be sutured with inverted Vicryl® 2.0 separate stitches. Finally, a suture of the skin with intradermal stitches (continuous suture) of Nylon 2.0 and a sterile dressing with gauze and adhesive tape will be done.

### Postoperative Care

In both groups, early active motion of the operated limb will be permitted as soon as motor function recovers from anesthesia. All participants will be instructed to begin immediate knee flexion and extension exercises, ankle and foot movements, and active calf pump exercises. No orthotic devices or physical positional measures will be utilized to restrict hip motion. However, all patients will be advised to avoid flexion, adduction, and internal rotation of the operated hip, or sitting in low chairs for at least 3 months. Walking with 2 crutches with weight-bearing as tolerated will be stimulated on the first postoperative day until the follow-up visit at 21 days, and patients will be discharged for ambulatory care as soon as ambulation is possible with comfort. Sports and activities on extreme hip motions will be discouraged for at least 3 months.

### Primary Outcomes

The primary outcomes of this study will be patient-reported function and complications.

Clinical evaluation will comprise the measurement of hip ROM to assess joint mobility, and the HHS questionnaire will be applied to assess function. Hip ROM will be measured using the goniometer, with the patient lying supine, to determine joint mobility. Hip function will be assessed using the HHS, which is a THA-specific questionnaire composed of patient-reported function and physician-assessed joint ROM, including pain, function, deformity, and mobility assessment [19,20]. The HHS is scored up to 100 points, where each section has a different score, and after applying the questionnaire, all scores are summed up. Scores below 70 are considered low, scores between 70 and 80 are considered fair, scores between 80 and 90 are considered good, and scores between 90 and 100 are considered excellent [19].

The incidence of complications (during and after surgery) will be extracted from an intraoperative questionnaire completed by the surgeon, an immediate postoperative questionnaire reported by the patient, and a special severe adverse effect questionnaire, which will be filled whenever the patient requires readmission or additional surgery.

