**Figure 1. F1:**
[figure not shown]
Flowchart of the study protocol. mHHS: modified Harris Hip Score; mo: months; SF-12: 12-Item Short Form Health Survey; wk: weeks; y: years; *: clinical evaluator; **: surgeon; ***: radiographic evaluator; ****: data curator (supervisor).

Standard digital anteroposterior pelvis radiographs with calibration spheres will be obtained. A clinical interview and thorough preoperative evaluation will be undertaken by a medical doctor (orthopedic surgery resident). Functional, pain, and QoL questionnaires will be administered at this point, and surgical appointments will be scheduled (Multimedia Appendix 1).

Patient assignment and preoperative evaluations will be conducted in monthly blocks of 12 patients for practical and logistic purposes. Random allocation of patients to each group, the HG and the UG, will be performed at this time using double blinding.

At this stage, the surgeon will be blinded to group allocation and clinical assessment and will perform surgical planning for both uncemented and hybrid procedures using Peekmed software (Peekmed Inc, Braga, Portugal). Peekmed is a highly sensitive tool currently in use that focuses on digital surgical planning to evaluate the accuracy of corrections and to reproduce patient-specific anatomy. Data from both surgical plans will be extracted by the same surgeon using a specially designed digital form (MultimediaAppendices 2  3). Reports of the surgical plans will be printed and kept until surgery; however, only the correct plan, as decided by the random group allocation, will be provided to the surgeon by the assistant researcher before surgery.

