### Secondary Outcomes

Secondary outcomes will include comparisons of QoL, joint mobility, function, satisfaction, and pain before and after the surgery, as well as radiographic parameters extracted from the immediate postoperative radiograph. The annual frequency of revision surgeries will be recorded.

QoL will be evaluated using 12-Item Short Form Health Survey version 2 questionnaire [21]. QoL is defined as an individual’s perception of their position in life in the context of the culture and value systems in which they live and about their goals, expectations, standards, and concerns [21]. The 12-Item Short Form Health Survey is an instrument for measuring QoL composed of 12 items that assess eight different dimensions of influence on QoL, considering the individual’s perception of aspects of their health in the last 4 weeks [21]. Each dimension’s score is summed up, and the final score can be between 0 and 100; the higher the score, the better the QoL [22].

Participant satisfaction assessment will be measured using a 10-point numerical rating scale ranging from 1 (very dissatisfied) to 10 (completely satisfied) [23].

Other aspects of health, such as pain, will be evaluated through the Visual Analog Scale. The Visual Analog Scale provides a simple and efficient measure of pain intensity and is used when a fast pain index that can be assigned to a numerical value is needed [24].

Radiographic parameters will include the ability to restore anatomical normality parameters on postoperative radiographs according to the surgical plan (namely the limb length discrepancy, the horizontal off-set of the hip, difference between the back of the prosthesis and the tip of the trochanter, inclination of the acetabular component, and the difference between offset obtained to the normal side) all of this using the Peekmed surgical planning software.

The annual frequency of revision surgery will be observed starting from 1 year after surgery and annually until 5 years, and up to 10 years.

All questionnaires will be administered by examiners blinded to the surgical procedure. Questionnaires will be completed using digital devices (computer or tablet).

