### Sample Size

The sample size was calculated using the Statulator Sample Size Calculation tool [25]. To disprove the null hypothesis of equality, assuming a pooled SD of 10.5 units for the HHS [6], the study would require a sample size of 60 participants per each group (ie, a total sample size of 120 for equal group sizes) to achieve a power of 80% and a significance level of .05 (2-sided) for detecting a true difference in means of 5.39 units between the test and the reference groups (ie, 56.9 vs 62.3).

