### Statistical Analysis

Results will be presented descriptively, with continuous data expressed as means (SD) and medians, and categorical data will be presented as means or percentages. For inferential analysis, the normality of the variables will be assessed using the Kolmogorov-Smirnov test. Dichotomous variables will be analyzed using the Fisher exact test and chi-square test, and continuous variables will be analyzed using the *t* test. Demographic data will be analyzed using ANOVA test, and the chi-square test will be used for the categorical data. In cases of non-normal distribution, appropriate nonparametric tests will be used according to the nature of the variable.

Primary outcomes, complications, and reoperations will be analyzed at 48 weeks. Paired and subgroup analyses are foreseen between periods of 3, 6, 24, and 48 weeks for the described outcomes. Results will be reported with 95% CI.

All statistical tests will be 2-sided, with a significance level of *P*=.05. Data will be analyzed using the Online Statistics Calculator, DATAtab/Numiqo (2025) [26]. Data from participants who receive additional treatments (eg, revision surgery for fractures) during study participation will be retained for intention-to-treat analysis.

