### Conclusion

This study is a prospective, randomized, pragmatic clinical trial that uses blinding to evaluate national implants for both hybrid arthroplasty and uncemented arthroplasty. It is the first study with adequate power to prospectively evaluate the outcomes of each surgical procedure in Brazil. Successful completion of this study may provide clinical evidence on the performance of national implants, as well as showing the preferred implant construct (hybrid or uncemented), if any, for hip replacement in Brazil.

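### HHS function and complications are both primary, each tested at two-sided .05 with no stated order or split; only HHS was sized, so the article's general claim of adequate power is unsupported for complications

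*Protocol article*

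**What the plan says.** All references are to the protocol article.

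- **Primary Outcomes** defines two: "The primary outcomes of this study will be patient-reported function and complications". The next paragraph, under the same heading, adds: "Clinical evaluation will comprise the measurement of hip ROM to assess joint mobility, and the HHS questionnaire will be applied to assess function".
- **Secondary Outcomes** lists some of the same domains again: "Secondary outcomes will include comparisons of QoL, joint mobility, function, satisfaction, and pain before and after the surgery".
- **Statistical Analysis** fixes one threshold: "All statistical tests will be 2-sided, with a significance level of" .05. Dichotomous variables go to Fisher's exact and chi-square tests, and primary outcomes and complications are analysed at 48 weeks. The section does not say how the two primaries combine into a conclusion.
- **Sample Size** is built on one variable, "assuming a pooled SD of 10.5 units for the HHS", with a difference of 5.39 units, 80% power and 60 per group. No complication rate, target difference or power appears anywhere in the article.
- **Conclusion** states: "It is the first study with adequate power to prospectively evaluate the outcomes of each surgical procedure in Brazil". The next sentence says that the trial may show a preferred construct, if there is one.
- **Figure 1 legend** expands an abbreviation as "mHHS: modified Harris Hip Score", whereas the Abstract, Primary Outcomes and Sample Size sections name the HHS.
- **Results** reports that a first analysis of the complete population, including early complications, was done in November 2025.

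**The concern.** Two primary outcomes at full alpha, with no rule joining them, give the trial two chances of a positive primary result. Unless both must succeed, or one is tested only after the other, the 5% level stated for each test is not the level for the set.

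The second issue is power. Complications are half of the primary objective and a main reason for comparing these constructs: the Introduction cites more periprosthetic fractures with uncemented stems. The sample size does not address them, yet the Conclusion claims adequate power without restricting it to HHS. A non-significant complications comparison published under that claim could be taken as evidence that the constructs are equally safe, when the trial had little chance of showing a moderate difference.

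The unsettled place of ROM and the two names for the hip score add to this, because they leave the primary function variable less than fully fixed.

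**Working it through.** **1. The plan's own figure.** Inputs from Sample Size: difference 5.39, SD 10.5, two-sided alpha .05, power 80%.

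n per group = 2 × (1.960 + 0.842)² × 10.5² / 5.39² = 2 × 7.849 × 110.25 / 29.05 = 59.6, rounded up to 60.

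Power at 60 per group is 80.3% by the normal approximation and 79.6% by the exact t-test. The HHS calculation reproduces.

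**2. False-positive rate over the two named primaries, if either can support a claim.**

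- Two independent tests of exact size 5%: 1 − 0.95² = 9.75%. Between two such tests, correlation lowers this to about 9.1% at 0.5 and 8.4% at 0.7.
- Fisher's exact test is conservative with few events. Enumerating all outcomes at 60 per arm gives its true size *a*. The combined rate, taking independence from HHS, is 1 − 0.95 × (1 − *a*). The common complication rates are assumptions, since the article gives none.

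| Assumed common rate | Fisher size *a* | HHS plus complications |
|---|---|---|
| 5% | 1.05% | 6.0% |
| 10% | 2.18% | 7.1% |
| 20% | 2.82% | 7.7% |

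The article also names the chi-square test, which is less conservative, so 9.75% is the nominal upper figure rather than the expected one.

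**3. Power for complications at 60 per arm, two-sided .05, all rates assumed.**

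| Rates | Fisher (exact enumeration) | Chi-square (approximation) | n per arm for 80% (chi-square) |
|---|---|---|---|
| 5% vs 10% | 9% | 18% | 435 |
| 10% vs 20% | 25% | 33% | 199 |
| 5% vs 15% | 33% | 45% | 141 |
| 5% vs 20% | 63% | 71% | 76 |
| 10% vs 30% | 73% | 79% | 62 |
| 5% vs 25% | 85% | 88% | 49 |

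Starting from 5% in one arm, 80% power needs about 24% in the other with Fisher (23.7% by enumeration) or 22.5% with chi-square.

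**4. What the remedies cost in HHS power.** Halving alpha to .025 for each primary drops HHS power at 60 per group to 71.6% (70.5% by the t-test); restoring 80% would take 73 per group, 146 in all. A fixed sequence with HHS first leaves HHS at .05, 60 per group and about 80%.

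**5. ROM.** The defining sentence names function and complications only. ROM appears under the same heading as part of the clinical evaluation of joint mobility, and joint mobility is then listed as secondary. The text does not settle which it is, so no calculation above counts ROM as a primary.

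**The case against.** The strongest reply is that the rule for claiming success is not stated. The article nowhere says that a preferred construct will be declared on whichever primary reaches P<.05; a reader might infer this, but the Conclusion says only that results may show a preference, if any. A .05 level per test in a condensed article is also compatible with a multiplicity rule in a full analysis plan that is not shown. This stands to the extent that the error-rate finding is conditional: it applies if either primary can support a claim, which the text neither states nor rules out. It does not rescue the power claim, which is printed without restriction.

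Three stronger readings should be resisted.

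- *Three primaries, with a false-positive rate of 1 − 0.95³ = 14.3%.* ROM is never named as a primary, so this figure does not apply.
- *The power claim is wrong for complications.* Without a complication rate in the documents, it can only be called unsupported.
- *Almost nothing could be detected.* A difference as large as 5% vs about 24% would be found with 80% power; it is moderate differences that would be missed.

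It can also be said that function reappearing among the secondary outcomes is no contradiction, because that sentence concerns comparisons before and after surgery and may mean within-patient change. That is fair, and the point does not rely on it. The modified HHS appears only as an abbreviation in the legend of a figure that is not shown, so it calls for harmonising the name and does not prove that a different score is used.

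**Conclusion.** The point holds in a limited form. Two primaries are named, each at two-sided .05, with no stated rule linking them. If either can support a claim, the false-positive rate over the pair is about 6.0% to 7.7% with Fisher's test for complications (common rates of 5% to 20% assumed, independence from HHS) and at most the nominal 9.75% for two independent tests of exact size 5%. That inflation is modest and would vanish under a both-must-succeed rule or a fixed order.

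The firmer part concerns power. The HHS sample size is correct on its own inputs, but it says nothing about complications, and under assumed rates Fisher power is 9% to 33% for absolute differences of 5 to 10 points. The Conclusion's general power claim should not stand as written. ROM's status and the name of the score are ambiguities to clear up and do not add to the error rate.

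**What to change.** 1. Make HHS at 48 weeks the first primary, tested at two-sided .05, with one version of the score (full or modified) named in the text, flowchart, forms and sample size.
2. Test complications at .05 only if HHS is significant. Otherwise report the risk difference with its 95% CI and no confirmatory claim.
3. List ROM as secondary only.
4. Restrict the power sentence in the Conclusion to HHS, and state that complications and revisions are estimated, not powered.

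**Cost.** No extra patients, and HHS keeps its full alpha and about 80% power. Complications lose stand-alone confirmatory status, which 60 per arm could support only for large differences. The change is more than a wording edit: the Results section reports that early complications were analysed in November 2025, and the article does not say whether by arm. Reordering the primaries after that analysis needs a dated amendment that discloses what had been seen, by arm, when the order was fixed.

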### Secondary Outcomes

Secondary outcomes will include comparisons of QoL, joint mobility, function, satisfaction, and pain before and after the surgery, as well as radiographic parameters extracted from the immediate postoperative radiograph. The annual frequency of revision surgeries will be recorded.

QoL will be evaluated using 12-Item Short Form Health Survey version 2 questionnaire [21]. QoL is defined as an individual’s perception of their position in life in the context of the culture and value systems in which they live and about their goals, expectations, standards, and concerns [21]. The 12-Item Short Form Health Survey is an instrument for measuring QoL composed of 12 items that assess eight different dimensions of influence on QoL, considering the individual’s perception of aspects of their health in the last 4 weeks [21]. Each dimension’s score is summed up, and the final score can be between 0 and 100; the higher the score, the better the QoL [22].

Participant satisfaction assessment will be measured using a 10-point numerical rating scale ranging from 1 (very dissatisfied) to 10 (completely satisfied) [23].

Other aspects of health, such as pain, will be evaluated through the Visual Analog Scale. The Visual Analog Scale provides a simple and efficient measure of pain intensity and is used when a fast pain index that can be assigned to a numerical value is needed [24].

Radiographic parameters will include the ability to restore anatomical normality parameters on postoperative radiographs according to the surgical plan (namely the limb length discrepancy, the horizontal off-set of the hip, difference between the back of the prosthesis and the tip of the trochanter, inclination of the acetabular component, and the difference between offset obtained to the normal side) all of this using the Peekmed surgical planning software.

The annual frequency of revision surgery will be observed starting from 1 year after surgery and annually until 5 years, and up to 10 years.

All questionnaires will be administered by examiners blinded to the surgical procedure. Questionnaires will be completed using digital devices (computer or tablet).

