**Objective:**

The aim of this study is to compare the clinical, radiographic, functional, pain, and QoL outcomes of patients who underwent surgery with a national hybrid prosthesis (with femoral cementation) versus patients who underwent surgery with a national uncemented prosthesis.

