While most RCTs in this area of research have traditionally focused on implant survival and revision rates [4], patient-centered outcomes, QoL, and early complications have become a current hot topic. Hybrid THA yields similar short- to mid-term patient-reported outcome measures (Harris Hip Score [HHS], WOMAC, EQ-5D) compared with cemented and uncemented constructs. A 2025 systematic review of 357,748 THAs found no difference in patient-reported outcome measures between hybrid and cemented THA and no clear advantage of uncemented constructs [11]. However, the incidence of periprosthetic fracture was reported to be significantly higher with uncemented stems, especially in older adults. Moreover, a slightly higher incidence of dislocations was also reported for uncemented stems [12]. Regarding pain, direct elective THA comparisons are limited, but evidence consistently shows more early pain and slower recovery with uncemented femoral fixation due to press-fit stem insertion forces. A meta-analysis of RCTs in THA showed better short-term pain scores with cemented fixation [13]. Additionally, a large National Health Service cost-effectiveness analysis (n≈300,000) found higher postoperative EQ-5D scores with hybrid THA (0.81 vs 0.80 for uncemented), and for most patient groups, hybrid prostheses were found to be the most cost-effective [14].

Few publications on THA performance using Brazilian-manufactured materials have reported results comparable to those from other countries; however, the level of evidence and sample sizes of these studies are limited [15-17]. Additionally, early failures of previous national models, commonly used in Brazil until the 1990s, became the reason for persistent questioning about the safety and durability of Brazilian-made implants [18]. To date, no level 1 study evaluating the performance of such implants in Brazil has been identified.

This study aims to compare the clinical outcomes (function, pain, complications, QoL, and need for revisions) and radiographic outcomes of patients treated with a national hybrid prosthesis (with femoral cementation and uncemented acetabular cup) versus those receiving national uncemented prostheses of the same brand.

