## Methods

### Study Design and Setting

This study was written according to the Standard Protocol Items: Recommendations for Interventional Trials (SPIRIT) guidelines (Checklist 1) for protocols of randomized clinical trials. The proposal is a single-center, single-surgeon, single-approach, pragmatic, double-blinded, prospective randomized trial to analyze the differences between uncemented hip replacement and the hybrid (femoral cemented) hip replacement.

Two different types of hip implants will be used for comparison: the Maxima Cemented Vincula Stem (Víncula, Rio Claro, SP, Brazil) and the Taper Uncemented Primary Stem (Víncula, Rio Claro, SP, Brazil). Patients and evaluators will be blinded to group allocation: the hybrid group (HG) and the uncemented group (UG). A total of 120 patients will be enrolled in this study and randomly allocated to each group in a 1:1 ratio.

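### The secondary outcomes are worded as before-versus-after and visit-to-visit comparisons, and the hybrid-versus-uncemented contrast that the trial asks about is not named for them

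*Protocol article*

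**What the plan says.** The Secondary Outcomes section of the protocol article gives the comparison for five domains: "Secondary outcomes will include comparisons of QoL, joint mobility, function, satisfaction, and pain before and after the surgery". Radiographic parameters and revision frequency are in the same section but are not worded as before-versus-after.

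The Statistical Analysis section says that "continuous variables will be analyzed using the *t* test", without stating whether that test is paired or independent or which outcomes it serves. It then adds: "Paired and subgroup analyses are foreseen between periods of 3, 6, 24, and 48 weeks for the described outcomes".

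The purpose of the trial is stated elsewhere as a comparison of arms. The abstract's Objective is to "compare the clinical, radiographic, functional, pain, and QoL outcomes of patients who underwent surgery with a national hybrid prosthesis" with those of patients given an uncemented one. The Introduction says: "This study aims to compare the clinical outcomes (function, pain, complications, QoL, and need for revisions) and radiographic outcomes", and contrasts "patients treated with a national hybrid prosthesis (with femoral cementation and uncemented acetabular cup) versus those receiving national uncemented prostheses". Study Design and Setting gives the purpose as "to analyze the differences between uncemented hip replacement and the hybrid (femoral cemented) hip replacement". The Sample Size section computes N for a difference between two groups: "To disprove the null hypothesis of equality".

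**The concern.** The two sentences that specify how QoL, mobility, function, satisfaction and pain will be compared both describe change within patients. A paired test of that kind has the null hypothesis of no change over time. The Introduction itself describes hip arthroplasty as highly successful in improving pain, function and QoL, and every participant receives one. That null is therefore expected to be false in both arms whichever stem is used.

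The Conclusion hopes to show which construct, if any, is preferred. An analysis that follows the secondary-outcome wording literally would produce small P values that cannot bear on that question. If paired tests between later visits were also run separately by arm, one arm could cross the threshold and the other not, and a reader could take that for a difference between implants.

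**Working it through.** **Inputs from the protocol article.** Sample Size: SD 10.5 for the Harris Hip Score, between-group difference 5.39, power 80%, two-sided 0.05, 60 per group. **Assumptions, not in the article:** the size of the change over time (3 to 20 points shown) and the correlation r between two visits (0 to 0.7).

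**1. The plan's own figure.** n per arm = 2(1.96 + 0.8416)² × 10.5² / 5.39² = 2 × 7.849 × 110.25 / 29.05 = 59.6, so 60. This reproduces the stated figure. Power at 60 per arm is 0.803 by the normal approximation and 0.796 by the noncentral t. The trial is sized for a between-arm contrast.

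**2. Before-after test within one arm, identical implants.** SD of change = 10.5 × √(2(1 − r)), which is 14.85, 12.42, 10.50 and 8.13 for r = 0, 0.3, 0.5 and 0.7. The chance of significance is about Φ(change × √60 / SD of change − 1.96). For 10 points at r = 0: 10 × 7.746 / 14.85 = 5.216, and Φ(3.256) = 0.9994.

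| Change over time | r = 0 | r = 0.3 | r = 0.5 | r = 0.7 |
|---|---|---|---|---|
| 3 points | 34.6% | 46.4% | 60.0% | 81.5% |
| 5 points | 74.2% | 87.6% | 95.8% | 99.8% |
| 10 points | 99.9% | 100% | 100% | 100% |
| 20 points | 100% | 100% | 100% | 100% |

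Only the ratio of change to SD matters. Ten points is 10 / 10.5 = 0.95 SD, so the third row applies to any scale on which surgery moves the mean by about one SD. The article gives no SD for the SF-12, pain, satisfaction or range of motion.

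**3. Between-arm test on the same data.** In 20,000 simulated trials per setting with identical arms (changes of 5 to 30 points, r = 0 and 0.5), an independent t test on the change or on the postoperative score was significant in about 4.5% to 5.2% of trials, as it should be.

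**4. Significance in exactly one of two identical arms.** If p is the chance in one arm, this is 2p(1 − p).
- 10 points, r = 0: simulated 0.1%.
- 5 points: simulated 39.8% at r = 0 (p = 0.727) and 9.2% at r = 0.5 (p = 0.952).
- 3 points: 2 × 0.346 × 0.654 = 45%, 2 × 0.464 × 0.536 = 50%, 2 × 0.600 × 0.400 = 48% and 2 × 0.815 × 0.185 = 30%, for r = 0, 0.3, 0.5 and 0.7.

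The expression cannot exceed 50%, which it reaches at p = 0.5. One-arm significance is therefore a hazard for small late changes, and is practically absent for a large before-after change.

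**The case against.** The strongest reply is that the between-arm comparison is already in the plan. The Objective and Introduction name function, pain and QoL as outcomes to be compared between hybrid and uncemented patients. Function, measured by the Harris Hip Score, is powered between groups. The t test in Statistical Analysis covers continuous variables in general and can be read as comparing the arms, with the paired analyses as extras. The before-and-after phrase may only describe when measurements are taken: the Recruitment and Preoperative Assessment section names functional, pain and QoL questionnaires before surgery but not satisfaction, so a literal before-after test of satisfaction has no stated baseline. A condensed article may also leave the exact model to a fuller document.

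Much of this stands. A reader might infer that these outcomes will not be compared between arms at all, or that the secondary analyses use no randomised contrast. The documents do not support that: nothing says that within-patient tests replace the group comparison. A reader might also infer a false-positive rate near 50%. That figure is the ceiling of 2p(1 − p). It needs small visit-to-visit changes, testing by arm and a misreading of the result, and the article does not say that paired tests will be run by arm.

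The reply does not remove the mismatch. The point is not a missing model: the article does state a comparison for these outcomes, and that comparison is over time. Function is already a primary outcome, so listing it again as secondary with before-after wording makes the within-patient reading a natural one. Paired ordinarily means within patient.

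**Conclusion.** The point holds as a mismatch between the objective and the stated secondary comparison. The sentences that specify the comparison for QoL, joint mobility, function, satisfaction and pain name change over time and no arm contrast; the stated aim and the general t test leave such a contrast open without fixing it.

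A before-after test with identical implants is almost certain to be significant: at least 99.9% per arm for a change of 10 points or more, with 60 per arm, SD 10.5 and correlations from 0 to 0.7. The change and the correlation are assumptions, and the SD is that of the Harris Hip Score only. For small changes between later visits significance is not assured (35% to 82% per arm at 3 points), and it may then appear in one arm only by chance. Neither result is evidence about the implants. The primary sample size is unaffected.

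**What to change.** In Secondary Outcomes, define each of the five outcomes as the between-group difference, hybrid minus uncemented, at 48 weeks with its 95% CI. This is the time point that Statistical Analysis already sets for the primary outcomes. Adjust for the preoperative value where one is collected. The article's text names function, pain and QoL questionnaires before surgery; satisfaction should be compared on the postoperative score unless a baseline exists.

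In Statistical Analysis, base inference at 3, 6, 24 and 48 weeks on between-group differences, for example from one repeated-measures model with a group-by-visit term. Report before-after and visit-to-visit changes per arm descriptively, without P values, and state that significance in one arm but not the other will not be read as a difference between implants.

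The cost is wording in two paragraphs. Patients, visits, data and the 60 per group stay as they are. The only loss is the within-arm P values, which do not inform the choice of construct.
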